**3.8 Unblinding procedure**

The PI or his deputy may ask the monitor to unblind an individual who develops a grade 3, 4 or 5 (death) SAE assessed as possibly related to the vaccination if it is in the volunteers best interest. The monitor may be asked to compile interim data for example for the regulatory authorities in Tanzania. Such data should remain blinded to the study staff and participants, but should be supplied to the DSMC. The DSMC will not be demanded to act on such data unless there are safety issues. When all volunteers have finished the DNA immunizations the monitor and statistician will compile group safety and immunological data while study staff and volunteers remain blinded.

**4 Assessments**

**4.1 Safety assessments**

The subject will be contacted the day after each immunization by the investigator, study nurse, or research assistant to obtain local and systemic reaction data and to determine the subject's clinical status.

Subjects will be instructed to call the specified study personnel immediately if any unusual or severe sign or symptom appears after immunization. These subjects should be seen in the clinic at the time of maximal symptoms, if possible, and will be followed up clinically until resolution of symptoms.

An adverse event is any undesired, noxious or pathological change in a patient or subject as indicated by physical signs, symptoms, and/or laboratory changes that occurs following administration of one of the vaccines, whether or not considered vaccine related. This definition includes intercurrent illnesses or injuries, and exacerbation of pre-existing conditions. The Steering Committee will arrange for a compilation of safety data when 10 subjects have received the electroporation. These data will be reviewed by the monitor for accuracy and submitted to the DSMC and Sponsor.

*4.1.1 Local adverse events*

Following the intradermal injections the site will be graded as dry, moist or wet. The presence or absence of a weal will be recorded. The pain will be recorded as none (0), mild (1), moderate (2), severe (3) or extreme (4). Following the electroporation the pain will be recorded as none (0), mild (1), moderate (2), severe (3) or extreme (4). Following the MVA pain in the muscle injected will be graded by the participant as none (0), mild (1), moderate (2), severe (3) or extreme (4).

This will be recorded in the appropriate case record form or once the participant has left the clinic, in the diary card.

Redness will be recorded as the maximum diameter in cm and graded on this criteria and the presence of symptoms according to the appended scale. Participants will be asked to record any discomfort and any medication taken for relief of symptoms.

Clinical staff will complete the case record form following eachimmunisation. Completed caserecord forms and the diary cards will be sent to the study nurse at Venhälsan to be recorded in the database. In the event that there are two observations on the same day, those confirmed at a visit will take precedence over diary card observations in the analysis.

Study personnel should verify all grade 3 or 4 events and record the findings in the source documents.

*4.1.2 Systemic adverse events*

Temperature will be measured by the oral route prior to immunisation and 30 minutes after the immunization by study personnel, and graded according to the appended scale. Participants will be given thermometers to record their temperature in the diary card on the evening of immunisation, and daily thereafter for 7 days, and if still raised, they will be advised to continue to monitor their temperature daily until it returns to normal. The temperature observed by the clinical team will be recorded on the case record forms for visits.

Chills, headache, nausea, vomiting, malaise and myalgia will be graded by the participants, recorded in the diary card on the evening following immunisation and daily for 7 days, or until resolution of symptoms whichever is longer. On days where a visit coincides with the diary card, the clinical staff will collect the information directly and record it in the case record form, and this will take precedence over diary card entries in the analysis.

Study personnel should verify all grade 3 or 4 events and document the findings in the source documents.

*4.1.3 Other adverse events*

These will be recorded as reported following an open question to participants, with the dates of commencement and resolution, and any medication required. They will be graded according to the general principles outlined. Social harm will also be recorded as an adverse event, graded according to the general guidelines.

Where a diagnosis is possible, it is preferable to report this rather than a series of symptoms relating to the diagnosis. When reporting a syndrome, indicate the associated signs and symptoms parenthetically following the syndrome rather than as separate events.

Study personnel should verify all grade 3 or 4 events and document the findings in the source documents.

*4.1.4 Routine laboratory, HIV serology and urinary parameters*

The following safety assessments will be undertaken in laboratories local to the clinical centre according to standard procedures subject to quality control.

Haematology: haemoglobin, white cell and platelet count, neutrophils and lymphocytes

Chemical pathology: liver function tests (AST/ALT, alkaline phosphatase, bilirubin), creatinine,

glucose

Immunology; CD4 number and percentage

HIV diagnostic testing: samples will be tested at SMI using ELISA and Western blot according to standard procedures subject to quality control

HIV serology for seropositivity will be performed as standardized for the clinic before and at the end of the study. In case of positive reactions, samples will be analyzed starting from the latest sampling and suspect positive reactions verified by PCR (viral load) at SMI according to standard procedures subject to quality control.

A mid-stream urine specimen will be collected for analysis.

Adverse events that are grade 3 and 4 or necessitate a physician's visit or a prescribed medication will be evaluated. The subject should be followed carefully until the condition is resolved and/or the cause is identified. Any medication or other therapeutic measure taken to relieve symptoms of the medical problem must be recorded on the appropriate case report form page(s) and in the source documents in addition to the outcome of the adverse event.

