| B2 | 10 | Id  ZetaJet® | electroporation | 1 inj 100µl  0,3 mg DNA* | 1 inj 100µl  0,3 mg DNA* | | 1 im inj needle  MVA 108 pfu |
|  | 2 | Id  ZetaJet® | electroporation | 1 inj 100µl saline | 1 inj 100µl saline | | 1 im inj needle  100µl saline |
| B3 | 10 | Id  ZetaJet® | electroporation | 1 inj 100µl  0,3 mg DNA* | 1 inj 100µl  0,3 mg DNA* | | 2 id inj Zetajet®,  tot. 0,6 mg DNA + electroporation |
|  | 2 | Id  ZetaJet® | electroporation | 1 inj100µl saline | 1 inj100µl saline | | 2 id inj Zetajet®,  tot 200µl saline +  electroporation |
| B4 | 10 | Id  ZetaJet® | electroporation | 1 inj100µl  0,3 mg DNA** mixed ampoules | 1 inj100µl  0,3 mg DNA** mixed ampoules | | 1 im inj needle  MVA 108 pfu |
|  | 2 | Id  ZetaJet® | electroporation | 1 inj100µl saline | 1 inj100µl saline | | 1 im inj needle  100µl saline |

*) 7 DNA plasmids **) 11 DNA plasmids.

Immunizations will be given as prime injections (HIV DNA) at weeks 0, 6 and 12 and as boost injections (MVA) at week 36 and week 60.

*2.4.2 Injections*

All **DNA** immunizations will be performed with a needle-free device, ZetaJet®, according to the manufacturer’s (Bioject Inc, Portland, Oregon) instruction.

Intradermal injections will be given over the deltoid muscle. Ampoule 1 will be given in the left arm and ampoule 2 in the right arm, except in the Group B4 where a mixture of vaccines from two identical ampoules will be given in both arms. Immediately after the injection subjects randomized to Groups B2, B3 and B4 will receive intradermal electroporation over the injection sites with the CytoPulse device, DermaVax, according to the manufacturer’s instruction.

All **MVA** injections will be performed with needle and syringe in the left deltoid muscle.

The site will be inspected after the immunisation, and any local reactions recorded on the case record form.

The immunisations will take place in an outpatient setting. Participants will be closely observed for 30 minutes after each immunisation, at which point vital signs (pulse, blood pressure and respiratory rate) will be recorded on the case record form, as well as any local or systemic reaction.

The needles, syringes and other materials will be disposed of according to local hospital regulations.

As with any parenteral vaccine, epinephrine and corticosteroids must be available for immediate use if an immediate hypersensitivity reaction, such as anaphylaxis, occur. Intravenous injections of vaccines will NOT be performed.

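### Read literally, the visit-over-diary rule in Sections 4.1.1 and 4.1.2 lets the 30-minute clinic record displace that evening's diary entry on every immunisation day

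*Protocol*

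**What the plan says.** For local reactions, Section 4.1.1 of the protocol states that, where there are "two observations on the same day, those confirmed at a visit will take precedence over diary card observations in the analysis". For systemic symptoms, Section 4.1.2 says: "On days where a visit coincides with the diary card, the clinical staff will collect the information directly". They enter it on the case record form, and "this will take precedence over diary card entries in the analysis". That sentence closes the paragraph on chills, headache, nausea, vomiting, malaise and myalgia. The separate temperature paragraph contains no precedence rule.

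Two sources exist on every immunisation day. Section 2.4.2 says: "Participants will be closely observed for 30 minutes after each immunisation, at which point vital signs" are put on the case record form, "as well as any local or systemic reaction". The diary then starts the same day. Temperature is to be entered "record their temperature in the diary card on the evening of immunisation, and daily thereafter for 7 days", and the other systemic symptoms are "recorded in the diary card on the evening following immunisation and daily for 7 days". Section 4.1.1 moves local recording to the diary once the participant has gone home.

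Section 1.5.1 makes solicited local and systemic events of grade 3 or above primary safety parameters. Sections 1.5.1 and 8.2 treat any grade 3 or 4 event as a sign that the group or arm tolerates its schedule less well.

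**The concern.** A rule that prefers clinician-confirmed findings to self-report is sensible when both describe the same reaction. On an immunisation day they do not: the clinic looks at 30 minutes and the participant reports hours later. If the clinic value is the one analysed for that date, a reaction that develops after the participant leaves is represented by an observation made before it began.

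The endpoint turns on single events in groups of ten vaccinees. One evening reaction of grade 3 that has subsided by the next entry could decide whether an arm is described as less well tolerated. The error runs in the favourable direction only.

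**Working it through.** No figure in the protocol depends on this rule, so there is nothing to reproduce. The check compares the visit schedule with the diary windows.

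1. **Where the rule can act.** Immunisations are at weeks 0, 6, 12, 36 and 60 (Section 1.2). The next scheduled visits are at weeks 2, 8, 14, 38 and 62 (Section 2.6), each 2 × 7 = 14 days after an immunisation. The diary covers days 0 to 7. The only scheduled visits inside a diary window are therefore the five immunisation visits themselves. Apart from unscheduled visits, the rule acts only on day 0.

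2. **Which record it keeps on day 0.** The clinic record is made at 30 minutes and the diary entry that evening. Visit precedence keeps the earlier of the two.

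3. **How many days.** 48 participants × 5 immunisations = 240 participant-days, of which 40 × 5 = 200 are on active product and 8 × 5 = 40 on placebo. This is an upper bound. Pain is graded in the clinic from none upwards, so a clinic value is expected each time. For other symptoms the protocol does not say whether a form with no reaction noted counts as an observation.

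4. **Direction.** Let c be the clinic grade and d the evening grade. The rule analyses c; the worst-grade alternative analyses max(c, d), which is never below c. Compared with that alternative, the rule can lower the day-0 grade but cannot raise it.

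5. **Sensitivity (illustration only; p and f are assumptions, not in the documents).** Let p be the risk per vaccinee of a reaction of grade 3 or above, and f the share of such reactions seen only in the day-0 evening entry and captured by no other route. The chance of at least one analysed event in 10 vaccinees is 1 − (1 − p(1 − f))^10.

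| p | f = 0 | f = 0.25 | f = 0.50 |
|---|---|---|---|
| 5% | 40% | 32% | 22% |
| 10% | 65% | 54% | 40% |
| 20% | 89% | 80% | 65% |

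The table shows how a one-event rule in small groups responds to lost entries. It does not estimate f, which could be close to zero.

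**The case against.** The best counter-argument is that the rule was written for something else. Section 2.4.3 brings in participants who report grade 2 or higher at next-day contact, and Section 4.1 asks for those with unusual or severe symptoms to be seen when symptoms are at their height. Those unscheduled visits fall in the diary window, and clinician precedence is reasonable there. An observation confirmed at a visit suggests the same reaction seen twice, and staff cannot collect an evening entry at 30 minutes. This probably describes the intention, and that use should be kept. But both sentences govern the analysis, neither carries the limit, and the systemic one applies whenever visit and diary coincide.

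A severe evening reaction also has other routes into the record: next-day contact, verification of all grade 3 or 4 events in source documents (4.1.1 to 4.1.3), and immediate reporting of related ones to the principal investigator (5.3). A reaction still present at the same grade on day 1 stays in the diary data. This narrows the exposure considerably. None of these provisions, however, is said to override the precedence rule.

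Three stronger readings are tempting but unsupported.

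- **That fever is overwritten.** Section 4.1.2 says "Temperature will be measured by the oral route prior to immunisation and 30 minutes after the immunization by study personnel", but the precedence sentence belongs to the next paragraph.
- **That day-0 evening reactions drop out of the primary endpoint altogether, or that a known share is lost.** The 240 days are 12.5% of 48 × 5 × 8 = 1,920 diary days, but that counts days and not events. Any resulting fall in the event rate rests on assumed inputs.
- **That the comparison of MVA with DNA plus electroporation as a boost is distorted.** That needs different onset profiles, on which the protocol gives no data.

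A statistical analysis plan may exist and was not available. The protocol does not leave this point open, though: it fixes a rule that such a plan would inherit.

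**Conclusion.** The concern holds as a defect in a stated analysis rule. Applied as written, it replaces the evening diary entry with the 30-minute clinic record on up to 240 participant-days, for local reactions and the six listed systemic symptoms. Those at risk of being understated are reactions that peak and subside on the evening of day 0 and are not captured by next-day contact or verification. The bias, where it occurs, is downward and affects a primary endpoint that responds to single events. Its size cannot be given from the documents. The conclusion rests on the literal wording and on the 30-minute record being treated as a visit observation; if the investigators meant only later symptom visits, a change of wording settles it.

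**What to change.** Replace the precedence sentences in Sections 4.1.1 and 4.1.2 with one rule. For each symptom and day, both the case record form and the diary entry are retained, and the highest grade from either source is analysed. A visit value overrides the diary only where it assesses the same episode at or after the diary entry. State that the rule also applies to temperature, and carry it into the analysis plan that Section 7.7.4 requires before the code is broken.

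The cost is a few sentences. Both records are already collected, so no new data are needed. The downside is that reported reaction rates may be slightly less favourable.

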**5.1 Definitions**

An adverse event is any adverse experience occurring during the course of the study including the screening period.

Criteria for grading clinical and laboratory events are listed in the appendix.

The severity of events reported on the adverse event form will be determined by the investigator, based on the Toxicity Grading Scale or if the event is not listed the event will be graded following these guidelines:

Mild (Grade 1): Transient or mild discomfort. No limitation in normal daily activity.

Moderate (Grade 2): Some limitation in normal daily activity.

Severe (Grade 3): Unable to perform normal daily activity.

Serious (Grade 4): Life threatening

Death (Grade 5)

A severe adverse event is one graded 3 or 4 by criteria in appendix. Some, but not all grade 3 and 4 adverse events will be “serious” by ICH GCP criteria below.

*5.1.1 Serious Adverse Events (SAEs)*

An adverse event is considered to be a “serious adverse event” by ICH Good Clinical Practice (ICH GCP) criteria if it results in the following:

- death,
- a threat to life,
- requires in-patient hospitalisation or prolongs existing hospitalisation (hospitalisation for elective treatment of a pre-existing condition is not included),
- results in persistent or significant disability or incapacity,
- is a congenital anomaly (i.e., the outcome of pregnancy involving a participant), or
- is any other important medical condition*.

*Examples of conditions regarded as “any other important medical condition” include allergic bronchospasm requiring intensive emergency treatment, seizures or blood dyscrasias which did not result in hospitalisation or development of drug dependency.

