**7.4 Monitoring**

The monitor will be recruited from Karolinska Trial Alliance, a Swedish study-independent centre with GCP educated professional staff specialized in study-associated services.

Karolinska Trial Alliance (KTA) [name], [name]

http://www.karolinskatrialalliance.se/

The monitor will be responsible for:

- Monitoring the trial according to ICH GCP guidelines including monitoring vaccine accountability, and dispatch and arrival of virological and immunological specimens
- Preparation of reports to assist the monitoring

The monitor will visit the clinical center to validate trial data against the clinical records. The monitoring will adhere to ICH Good Clinical Practice guidelines. The following data should be verifiable from source documents:

- completeness of the study file including all approvals, CVs etc
- documentation of any existing conditions or past conditions relevant to eligibility
- signed consent
- dates of visits including dates of immunisations
- source verification of all laboratory data which are out of the normal range entered into the data base
- source verification of all grade 2 or above adverse events entered into the data base

and any events leading to discontinuation of the immunisation schedule

Vaccine returns will also be monitored at visits to the clinical centre/pharmacy*.*

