**8.2 Analysis**

All safety end-points will be graded by the Clinical Investigator and reviewed by the Trial Management Group. Any queries about grade and relationship to study product that cannot be resolved will be referred to the Trial Coordinating Committee for a final decision.

The primary end-points:

1. The safety of immunization with the seven or eleven DNA plasmids carrying HIV-1 genes will be assessed by clinical signs and standard biochemical and haematological laboratory tests where any worsening of the severity grade will be considered for causality with the vaccine.
2. The immunization will be evaluated by assessing local (pain, cutaneous reactions including induration), general (fever, chills, headache, nausea, vomiting, malaise, myalgia) and other unsolicited adverse events within 7 and 28 days. Any grade 3 or 4 event will be taken as an indication that the arm is less tolerable.

The secondary endpoints

The secondary endpoint (immunogenicity) will primarily be assessed by IFN-γ ELISpot 2 weeks after the third DNA immunization, the fourth DNA or first MVA immunization and after the fifth DNA or second MVA immunization. Both number of responders and magnitude of responses will be tested for significance. Additional studies will be performed at other time points using other assays such as intracellular cytokine staining, lymphoproliferation assays, epitope mapping, binding (and if indicated) neutralization antibody assays.

Group B1 will be compared with the id only group in the HIVIS study (Group A in HIVIS trial) for evaluation of the lower dose of HIV DNA (0.6 vs 1.0 mg).

Group B2 will be compared with Group B1 for evaluation of the lower dose of HIV DNA with and without electroporation.

Group B3 will be compared to the group B2 for the evaluation of HIV DNA as a boost compared to boosting with HIV MVA.

Group B4 is will be compared to groups B1-B3 to show if priming with additional HIV-related plasmids will increase immunogenicity to any of the included antigens.

Figures/tables will be prepared including all participants’ results.

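### Solicited reactions have two graders, and the protocol does not say whose grade enters the primary grade 3/4 tolerability rule

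*Protocol*

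**What the plan says.** Three parts of the protocol say who grades.

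- Section 4.1.2, systemic reactions: "Chills, headache, nausea, vomiting, malaise and myalgia will be graded by the participants", on the diary card, from the evening of immunisation and daily for 7 days or until resolution. Section 4.1.1, local reactions: "Following the MVA pain in the muscle injected will be graded by the participant". Section 4.1.1 names no grader for pain from the intradermal injection or from electroporation.
- Section 5.1: "The severity of events reported on the adverse event form will be determined by the investigator, based on the Toxicity Grading Scale".
- Section 8.2: "All safety end-points will be graded by the Clinical Investigator and reviewed by the Trial Management Group". Unresolved queries about grade go to the Trial Coordinating Committee. Section 7.6.1 gives final decisions on grade to the Steering Committee.

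Sections 4.1.1 and 4.1.2 each add that, where a visit and a diary entry fall on the same day, the visit record prevails in the analysis.

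On checking, section 4.1.1 says "Study personnel should verify all grade 3 or 4 events and record the findings in the source documents", and 4.1.2 repeats this for systemic events. Section 7.4 lists "source verification of all grade 2 or above adverse events entered into the data base" among the items that the monitor must be able to verify.

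Sections 1.5.1 and 8.2 list the solicited local and systemic symptoms within the primary endpoint and treat one grade 3 or 4 event as an indication of lower tolerability. The synopsis blinds the laboratory to groups B1 to B3, and blinds clinic and laboratory to the controls within each group.

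**The concern.** The same symptom has two graders, and the outcome is a threshold on the grade. A headache that a participant scores 3 and the investigator scores 2 flags the arm under section 4.1.2 but not under section 8.2. The reverse disagreement has the opposite effect. With ten vaccinees per arm and a rule triggered by one event, one such case can decide the primary tolerability statement.

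Two features make disagreement more than a clerical matter. The explicit staff check applies to high grades only, so high and low reports are not re-examined equally. And the staff who would regrade can see whether the participant was electroporated, which is the feature whose tolerability is the primary question.

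**Working it through.** The protocol gives no figure on this point, so the check is a comparison of the text, followed by an illustration with assumed rates.

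**1. Do both grading rules cover the same events?** Yes. Chills, headache, nausea, vomiting, malaise and myalgia are named in section 4.1.2 as participant-graded and in sections 1.5.1 and 8.2 as primary endpoint items. Section 8.2 assigns every safety endpoint to the investigator, without exception.

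**2. Is the diary grade only raw material for the investigator?** The text points the other way. The same-day rules say that visit records override diary entries in the analysis. Such a rule is needed only if diary grades otherwise enter the analysis.

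**3. Does the same-day rule settle the conflict?** Rarely. The diary runs 7 days. In the flow chart (section 2.6), immunisations are at weeks 0, 6, 12, 36 and 60, and the next scheduled visits are at weeks 2, 8, 14, 38 and 62, each two weeks later. The only scheduled overlap is immunisation day itself. Section 2.4.2 has staff record local and systemic reactions after 30 minutes of observation, while the first diary entry for symptoms is made that evening. Read literally, the earlier clinic record displaces the later diary grade. Any other overlap depends on an unscheduled visit.

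**4. Which grades are checked?**

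| Check | Starts at | Section |
| --- | --- | --- |
| Verification by study personnel | grade 3 | 4.1.1, 4.1.2 |
| Clinic visit prompted at the day-after contact | grade 2 | 2.4.3 |
| Weekly Trial Management Group discussion, related events | grade 2 | 5.3 |
| Monitor's source verification | entered as grade 2 | 7.4 |

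A reaction entered as grade 1 is outside all four. What follows if a solicited grade 3 is not verified is not stated. Section 1.5.1 attaches a confirmation condition only to other clinical or laboratory events.

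**5. Who knows what?** Groups B2, B3 and B4 receive electroporation and B1 does not (section 2.4.2). Clinic staff therefore see the group. By design they do not know vaccine from saline within it.

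**6. Scale (all rates assumed).** Let *p* be the proportion of vaccinees with a participant-graded grade 3/4 reaction, and *d* the proportion of those who are downgraded. For an arm of 10,

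P(arm flagged) = 1 − (1 − p(1 − d))^10.

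| p | d = 0 | d = 25% | d = 50% |
| --- | --- | --- | --- |
| 2% | 0.18 | 0.14 | 0.10 |
| 5% | 0.40 | 0.32 | 0.22 |
| 10% | 0.65 | 0.54 | 0.40 |
| 20% | 0.89 | 0.80 | 0.65 |

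For example, 1 − 0.90^10 = 0.651 and 1 − 0.95^10 = 0.401. The table ignores upgrades. Suppose instead that 25% are downgraded, that grade 2 reactions occur at rate 2p, and that 12.5% of those are raised to 3. The rate is then 0.75p + 0.125 × 2p = p, and every probability returns to its d = 0 value.

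**The case against.** It can fairly be said that sections 4.1.1 and 4.1.2 describe capture, that section 8.2, being the analysis section, describes adjudication, and that a committee settles disputes. The case report forms and grading scale are in appendices that are not shown, and an analysis plan may exist. The trial is descriptive, and all participants' results will be tabulated. Participants also know whether they were electroporated, so preferring their grade does not remove knowledge of the group.

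The last point stands, and it is a reason to report both grades. The capture-then-adjudicate reading does not survive the same-day rules, which presuppose that diary grades are analysed. The committee route does not settle matters either, because sections 7.6.1 and 8.2 name different committees. An analysis plan could choose between two recorded grades, but it could not recover one that had been overwritten.

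A reader might go further and infer that the grade 3/4 count can only be moved down, by staff who know the treatment. The documents do not support that:

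- The visit-over-diary rules apply at every grade and can raise one.
- A grade 2 report the day after injection prompts a visit at which it may become a 3.
- Diaries are discussed before the next injection with no grade threshold (section 2.4).
- Investigator grading has no floor.
- No section says that an unverified grade 3 is lowered; verifying is not regrading.
- Checks other than staff verification start at grade 2.
- Staff know the group, not vaccine versus saline.

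**Conclusion.** The contradiction over the grader is real and bears directly on the primary tolerability rule. Sections 4.1.1 and 4.1.2 make the participant the grader of MVA-site pain and six systemic symptoms; section 8.2 makes the investigator the grader of all safety endpoints, as 5.1 does for events on the adverse event form. Outside same-day visits nothing says whose grade counts, and the same-day rule itself can replace an evening diary grade with a reading taken about 30 minutes after injection.

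Because checking is uneven across grades and staff can see the group, regrading could bias the count, possibly by different amounts in electroporated and non-electroporated arms. Neither direction nor size is fixed by the protocol. The fall from 0.65 to 0.40 is an illustration that rests on an assumed 10% rate, assumed 50% downgrading and no upgrades. This should be corrected before data capture.

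**What to change.** Reconcile sections 4.1, 5.1 and 8.2 as follows.

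- Name one analysed grade for solicited reactions, for example the worst grade per immunisation across diary and visit records. Word 8.2 and 5.1 to match, and name a grader for injection and electroporation pain.
- Amend the same-day rules in 4.1.1 and 4.1.2 so that a visit record does not erase a later or higher diary entry.
- Keep the participant's original grade and the investigator's grade in separate fields, neither overwriting the other, whichever way they differ.
- Report the grade 3/4 count by arm under both grades.
- Name one committee for final decisions on grade in 7.6.1 and 8.2.

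Optionally, let the monitor check all diary entries of a small random sample of participants, whatever the entered grade.

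The cost is protocol wording, one extra database field and one extra table; the optional check adds a few monitor hours. The drawback is that a mis-graded diary entry stays visible, with the verified grade beside it.
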